### Interventions

2.6

1.Establishment of ECMO: The surfaces of all connecting pipes of the ECMO system, the contact surfaces of the oxygenator and the centrifugal pump are all covered with heparin coating. After ultrasound assessment of blood vessel diameter and elastic plaque, the femoral vein (20–22 Fr) and femoral artery (16–20 Fr) were inserted percutaneously. If severe ischemia occurs in the lower extremities, place a 6F perfusion tube to increase blood supply to the lower limbs. The perfusion tube increases blood supply to the lower extremities. The femoral vein femoral artery catheterization was used to establish an ECMO (Veno-arterial Extracorporeal Membrane Oxygenation) support model.2.ECMO management: ①Adjust pump flow according to cardiac function and hemodynamic parameters; ②Anticoagulation management: use unfractionated heparin for anticoagulation, monitor the activated coagulation time every 2 hours, and adjust the amount of heparin to maintain it between 160 and 200 seconds; ③Mechanical ventilation management: mechanically assisted ventilation according to protective lung ventilation strategies; ④Hemodynamic management: monitor heart rate, blood pressure of right upper limb, blood oxygen saturation of right hand. Measure blood gas and central venous oxygen saturation at 4 hour intervals; ⑤Management of vasoactive drugs: adjust the type and dosage of vasoactive drugs according to circulatory indicators such as blood pressure and heart rate.3.CRRT establishment: In ECMO combined with CRRT treatment, if the 2 loops are placed separately, it will inevitably increase the risk of bleeding and infection, and there are problems such as expensive and complicated operations.^[10]^ The current conventional method is to add the CRRT machine to the ECMO loop, which can avoid the risk of multiple tube placement. When ECMO is combined with CRRT treatment, the connection method of the pipeline is to join the CRRT loop in parallel on the ECMO pipeline. The inlet end (artery) of CRRT is connected to the back end of the centrifugal pump through a three-way connection, and the outlet end (venous) is connected to the other end is before the membrane lung.^[11]^ Choose continuous venous-venous hemofiltration or diafiltration mode, the replacement dosage is pre-dilution (or dialysis) 1 to 2 L/hour, post-dilution 1 L/hour, replacement fluid and dialysate use modified port formula replacement fluid. The nurse adjusts the pump speed according to the doctor's advice according to the acid-base level of the blood gas analysis; adjusts the potassium chloride dosage according to the blood potassium level. Soak and flush the pipeline with 0.9% sodium chloride solution. No additional anticoagulant measures are added during CRRT.4.ECMO weaning indication:^[12]^ ECMO assisted flow rate is reduced to 1 L/min, no or only small doses of vasoactive drugs are used to maintain hemodynamic stability, mean arterial pressure >60 mm Hg (1 mm Hg = 0.133 kPa), Pulse pressure difference >20 mm Hg, LVEF(left ventricular ejection fraction)>35% to 40%, central venous pressure <10 mm Hg, left ventricular pressure <12 mm Hg, systemic central venous oxygen saturation >65% to 70%, lactic acid <2 mmol/L.5.Nursing intervention: The operation of the machine and the setting of parameters should be closely monitored in nursing. The nurse observes and records the speed and flow rate of the centrifugal pump every hour, and observes the pressure before and after the pump to avoid hemolysis caused by excessive negative pressure; observe the pressure before and after the oxygenator, observe whether the pipeline shakes, the color of the pipeline, and whether the flow rate is suddenly high suddenly low to prevent insufficient blood flow, thrombosis or pericardial tamponade, etc.; check the temperature setting of the water tank and actual water temperature, etc.; closely monitor heart rate, heart rhythm, blood pressure, urine output, bedside electrocardiogram, left ventricular systolic function and change trends; use blood purification A dedicated observation record sheet, which accurately records data such as arterial pressure, venous pressure, filtrate pressure measurement, transmembrane pressure, pressure drop, fluid flow in and out, and dehydration volume every hour. In any case, inform the responsible doctor as soon as possible.

The treatment group adopts the combined treatment mode of ECMO and CRRT, and the control group adopts the ECMO treatment mode. Any emergencies during treatment will be dealt with according to the expert consensus opinion of fulminant myocarditis.^[9,13]^ All nurses and doctors involved in the treatment are experienced professionals.

### Observation indicators

2.7

1.Record the patient's basic vital signs changes (such as blood pressure, body temperature, heart rate, etc.), weaning time, hospital stay, etc.;2.Monitor changes in laboratory indicators before and after treatment: such as N terminal pro B type natriuretic peptied, high-sensitivity troponin I, myocardial enzymes, oxygenation index (partial pressure of O_2_/fraction of inspiration O_2_), blood lactic acid (lac), liver and kidney function, coagulation function, arterial blood pH, etc.;3.Echocardiographic indicators: left ventricular ejection fraction (LVEF), left ventricular end-diastolic diameter;4.Complications and treatment outcomes: including weaning rate, in- and out-of-hospital mortality, complication rate (such as infection, bleeding, thrombosis, etc.).5.Sequential Organ Failure Assessment (SOFA)^[14]^ score is used to assess the patient's organ condition.

### Data collection and management

2.8

Observation indicators were collected before treatment, 24 hours, 48 hours, 72 hours, 96 hours after treatment, and 2 hours before weaning. At the same time, follow-up for 30 days to assess complications and treatment outcome. One or 2 assistants will collect and record the entire data. Personal information about potential participants and registered participants will be collected, shared and stored in an independent storage room to protect confidentiality before, during and after the test. The access to the database will be restricted to the researchers in this study team.

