## Discussion

3

Patients with fulminant myocarditis progress rapidly and are often accompanied by difficult to correct hemodynamic disturbances or stubborn fatal arrhythmias. Therefore, the early use of effective mechanical assist devices is the key to improving the prognosis of such patients.^[3,15]^ It has been reported in the literature that the survival rate of mechanical assist devices for fulminant myocarditis is 57% to 80%.^[3,16]^ Early and timely ECMO placement to maintain effective circulatory perfusion is the key to reducing the mortality of FM. However, for long-term use of ECMO treatment, it should be noted that the probability of complications of ECMO treatment such as limb ischemia, abnormal coagulation function, bleeding, and infection will be greatly increased.^[17]^ Some researchers believe that ECMO combined with CRRT avoids the risk of bleeding at the puncture site during ECMO-assisted systemic anticoagulation. At the same time, it can measure the pressure of the ECMO membrane before and after the membrane, reduce the pressure measurement device, and reduce the risk of infection.^[18]^ Studies have shown that during EMCO treatment, about 50% of patients may be combined with CRRT treatment,^[19]^ which may be related to ECMO oxygenated blood flowing backward through the renal artery, ECMO-related inflammation activation, high anticoagulation state, hemolysis, etc. These factors are related.^[20]^ The integrated use of ECMO and CRRT in parallel can achieve joint support of multiple organs such as heart, kidney, and lung in 1 cardiopulmonary bypass pathway. However, some scholars believe that the use of CRRT during ECMO may increase the risk of in-hospital mortality.^[21]^ Therefore, whether the early application of CRRT is beneficial to the prognosis of patients with fulminant myocarditis still needs clinical research to verify.

This study also has the following limitations: the sample size included in this study is limited, which may affect the results. The planned follow-up time for this study is short, and there is no assessment of the long-term efficacy and safety of the treatment plan. If necessary, we will extend the follow-up time and pay more attention to its long-term efficacy.

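### Values taken 2 hours before weaning exist only for patients who reach weaning, and for LVEF, lactate and blood pressure the weaning criteria constrain them, so they should be described and not tested

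*Protocol article*

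**What the plan says.** Section 2.8 (Data collection and management) sets the sampling times: "Observation indicators were collected before treatment, 24 hours, 48 hours, 72 hours, 96 hours after treatment, and 2 hours before weaning". All but the last follow the clock.

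Section 2.6, item 4, gives the indication for weaning from ECMO. Among other conditions it asks for "mean arterial pressure >60 mm Hg", "LVEF(left ventricular ejection fraction)>35% to 40%, central venous pressure <10 mm Hg, left ventricular pressure <12 mm Hg" and "lactic acid <2 mmol/L".

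Section 2.7 lists what is observed. Blood pressure is among the vital signs. The laboratory list includes "blood lactic acid (lac), liver and kidney function, coagulation function, arterial blood pH". Item 3 reads "Echocardiographic indicators: left ventricular ejection fraction (LVEF), left ventricular end-diastolic diameter", and SOFA is item 5. Weaning time, weaning rate and mortality are recorded too, so the protocol itself expects that some patients will not be weaned.

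Section 2.9 compares measurement data between groups by t test or Mann–Whitney U and within groups by paired t test, two-sided at P < .05. It names no time points and excepts none.

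**The concern.** A value taken just before weaning is conditional on an outcome of treatment. Two problems follow.

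- **Indicators that are weaning criteria** (LVEF, lactate, arterial pressure). Patients are sampled when they are about to satisfy the same thresholds in either arm. Faster recovery then shows as earlier or more frequent weaning, and hardly at all in the value at weaning. A non-significant result could be read as equal cardiac recovery when recovery differs. In a paired test from baseline, the rule that defines the time point supplies much of the improvement.
- **Indicators outside the criteria** (for example SOFA, kidney function, LVEDD, troponin). The thresholds do not act on them directly, but the comparison is confined to a subset formed after randomisation and is made after unequal time on support.

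**Working it through.** **No planned figure to reproduce.** Section 2.3 sets at least 40 per group by reference to similar studies, without an effect size, SD or power. The point does not depend on that number.

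**1. Overlap of indicators and criteria.** Setting section 2.7 beside section 2.6, item 4:

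- In both: LVEF, lactate, arterial pressure.
- Observed but not criteria: NT-proBNP, troponin, myocardial enzymes, oxygenation index, liver and kidney function, coagulation, pH, LVEDD, SOFA.

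The criteria are one-sided (above for LVEF and pressure, below for lactate). They constrain the values without fixing them.

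**2. Masking of a criterion variable (simulation A; every input assumed).** 3,000 trials, 40 per arm; baseline LVEF mean 22, SD 5; slope SD 1.5 points/day; measurement SD 2; weaning at the first 12-hourly LVEF above 37.5% (the middle of the protocol's 35% to 40%); death hazard 0.07/day in both arms; 14-day horizon. Two-sided t test at 0.05.

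| Mean slope, points/day | LVEF at 72 h, all patients: difference (rejection) | LVEF at 72 h, alive and still on ECMO | LVEF at weaning, weaned only |
|---|---|---|---|
| 3.5 vs 2.5 | 2.97 (46.6%) | 2.24 (27.9%) | 0.17 (6.4%) |
| 3.0 vs 2.5 | 1.45 (14.5%) | 1.09 (9.6%) | 0.09 (5.7%) |
| 2.5 vs 2.5 | 0.02 (5.2%) | 0.00 (4.9%) | -0.01 (4.5%) |

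The 72 h column for all patients gives a value even to those who died earlier, so it is an ideal. The column for patients still supported is nearer to what would be seen. With a real effect, the test at weaning rejects at about its null rate.

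**3. Sensitivity (simulation B; other assumed inputs, no deaths).** Baseline LVEF 20, SD 6; slopes 3 vs 2 points/day, SD 1; measurement SD 1.5; 15-day horizon. The true difference at 96 h is (3 - 2) × 4 = 4.0 points. With cut-offs of 35% to 40% and readings every 4 to 24 h, the difference is about 0.1 to 0.3 points at the reading that triggers weaning, and about 0.2 to 0.45 points at a separate reading 2 h earlier. It stays small throughout.

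**4. Indicators outside the criteria (simulation A with a second marker that plays no part in weaning).**

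- Real effect (3.5 vs 2.5 points/day on the marker too): difference 3.02 at 72 h (rejection 50.2%) against 2.28 before weaning (9.7%). It is blurred, not removed.
- No recovery effect, death hazard 0.03 vs 0.10/day: weaned 70% vs 48%; difference -0.02 at 72 h against 1.29 before weaning (rejection 5.3%). The arm with fewer deaths weans on average 0.52 days later, and 0.52 × 2.5 points/day = 1.30. The gap therefore comes from unequal time on support. LVEF itself differs by -0.02 before weaning.

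**5. Loss of patients.** The article gives no share weaned. Its nearest figure is in the Discussion: "survival rate of mechanical assist devices for fulminant myocarditis is 57% to 80" per cent. If, as an assumption, the weaned share lay in that range, 40 × 0.57 ≈ 23 to 40 × 0.80 = 32 patients per arm would have the value. The difference detectable with 80% power is (1.960 + 0.842) × √(2/n) SD:

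- n = 40: 0.63 SD
- n = 32: 0.70 SD
- n = 23: 0.83 SD

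**The case against.** **The test is not named.** Section 2.8 is a collection schedule, and section 2.9 never says that arms are compared before weaning. A condensed article may leave the choice of time points to an analysis plan. It is true that the comparison follows from general wording and not from an explicit statement. But the article fixes both the time point and tests for measurement data without exception, so following it as written includes this comparison. A within-group before-and-after reading does not escape the problem, because the paired test is affected too.

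**Stronger readings that a reader might infer.** One is that all pre-weaning values are fixed by the criteria. Only three of the named indicators are criteria, and those are bounded on one side. Nor does the article say that every criterion was already met at the sample 2 hours earlier. Another is that the comparison is one of survivors and is demonstrably biased for every indicator. Patients who reach weaning may still die within the 30 days of follow-up, and the selection scenario above gave a shifted mean with near-nominal rejection. A third is that 20% to 43% of patients will die without this value. The survival range concerns mechanical assist devices in the literature and is not the share weaned on ECMO.

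**Other data remain.** Weaning rate, weaning time, mortality and the four fixed times could all show an effect, and nothing makes the pre-weaning value a key endpoint. This stands: the test can hide an effect at that time point, but it does not hide the effect from the trial.

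**Fixed times are not clean either.** In simulation B, 14% to 17% vs 5% to 7% are already weaned by 96 h at a 40% cut-off, so 96 h mixes supported and unsupported patients. This also stands, and it is why deaths and numbers weaned belong beside each fixed-time comparison.

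**Conclusion.** The point holds in a limited form. For LVEF, lactate and arterial pressure, a between-arm test 2 hours before weaning can be nearly blind to a real difference in recovery, and a paired test from baseline shows improvement largely by construction. For other indicators the comparison is restricted to a subset selected after randomisation and made at unequal times on support; the size and direction of any bias are unknown.

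The direction of the masking follows from the weaning rule. Its size, 3 to 4 LVEF points at a fixed time against about 0.1 to 0.5 before weaning, rests on assumed baselines, slopes, noise and reading intervals and is illustrative. Only LVEF was simulated as a criterion variable; lactate and blood pressure rest on the same reasoning. This is a cheap improvement to the analysis wording and does not invalidate the trial.

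**What to change.** Add to section 2.9:

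- Values taken 2 hours before weaning are reported descriptively, with the number of patients contributing in each group. They are not tested between groups and do not serve as the after value in paired tests.
- Between-group comparisons of indicators use the fixed 24, 48, 72 and 96 h values. The number who have died and the number already weaned are reported by group at each time.
- Weaning is compared through outcomes already collected: weaning rate, mortality, and time to weaning with death as a competing event.

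No sample, visit or clinical rule changes. The cost is a few sentences of analysis wording and one fewer tested time point.

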### Statistical analysis

2.9

The SPSS 25.0 software was used for statistical analysis. Measurement data are expressed as mean ± standard deviation or median (quartile), and count data are expressed as number of cases. The independent sample *t* test or Mann–Whitney *U* test was used for the comparison of measurement data, the paired *t* test was used for the comparison within the group, and the Chi-Squared test or Fisher exact probability method was used for the comparison of count data. All are two-sided tests, with *P* < .05 as the difference is statistically significant.

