### Sample size

2.3

In order to draw reliable conclusions, this study will include as many qualified samples as possible, referring to similar studies,^[8]^ we set the minimum number of people in each group of studies to 40, and the final number will be based on actual recruitment.

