### Study design

2.5

Eligible participants were randomly assigned to the treatment group or the control group at a ratio of 1:1 using a random tool based on the central network. Randomization was performed without any stratification generated by an independent statistician who was not involved in trial implementation or statistical analysis using SAS 9.3 software (SAS Institute, Cary, NC). The clinical research coordinator entered the participant information on the tablet, and was given a random number. The research assistant gets the participant's assignment from the computer. Throughout the research process, the research assistant is responsible for screening, recruiting participants, and assigning random numbers to the included participants. The result assessor is responsible for the assessment of the scale.

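### Within-group paired t tests do not compare the randomised arms; a between-arm estimate adjusted for the pre-treatment value is easier to interpret and, if the correlation is moderate, more precise

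*Protocol article*

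**What the plan says.** Section 2.9 (Statistical analysis) names two kinds of test for continuous data. Between arms: "The independent sample *t* test or Mann–Whitney *U* test was used for the comparison of measurement data". Within each arm: "the paired *t* test was used for the comparison within the group". One significance rule covers them all: "All are two-sided tests, with *P* < .05 as the difference is statistically significant". No covariate is named. The section does not say whether the between-arm test is run on follow-up values or on changes, or what the within-group tests are for.

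Section 2.8 (Data collection and management) provides a pre-treatment value and repeated follow-up: "Observation indicators were collected before treatment, 24 hours, 48 hours, 72 hours, 96 hours after treatment, and 2 hours before weaning". Section 2.7 describes the laboratory indicators in terms of change from before to after treatment.

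Allocation is 1:1 (Section 2.5), and "Randomization was performed without any stratification". On size, Section 2.3 says "we set the minimum number of people in each group of studies to 40". Section 2.6 gives ECMO to both arms and CRRT to the treatment arm only.

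**The concern.** The trial asks what CRRT adds to ECMO. A paired test inside one arm answers a different question: whether that arm changed. The change mixes ECMO support, the natural course of the illness, regression to the mean and the loss of patients who die. Finding P < .05 in one arm and not in the other is not a comparison of the arms, yet placing the paired tests beside the between-arm tests under one significance threshold invites that reading.

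Separately, the trial is small and unstratified and records a pre-treatment value for its indicators, but the named between-arm tests do not use that value as a covariate. At stake is precision that could be had from data already planned.

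**Working it through.** **Inputs from the protocol article.** Two-sided alpha 0.05 (Section 2.9); 1:1 allocation (Section 2.5); minimum n = 40 per arm (Section 2.3). No effect size, SD, power or baseline-to-follow-up correlation r is given, so 40 per arm cannot be reproduced. For scale only, a normal approximation gives 80% power at a difference of √(2/40) × (1.960 + 0.842) = 0.626 SD.

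**Assumptions.** The common within-arm change d, in SDs of the paired differences, runs from 0.1 to 0.8. The correlation r runs from 0 to 0.7. Outcomes are standardised to SD = 1.

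**Step 1: paired tests when the arms do not differ.** Let p be the power of one paired t test with n = 40: noncentral t, 39 df, noncentrality d√40, critical value 2.023. The arms are independent, so the chance that exactly one is significant is 2p(1 − p).

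| d | p | 2p(1 − p) |
|---|---|---|
| 0.1 | 0.095 | 17% |
| 0.2 | 0.235 | 36% |
| 0.3 | 0.457 | 50% |
| 0.4 | 0.694 | 42% |
| 0.5 | 0.869 | 23% |
| 0.6 | 0.959 | 8% |
| 0.7 | 0.991 | 2% |
| 0.8 | 0.998 | 0.3% |

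For example, at d = 0.4: 2 × 0.694 × 0.306 = 0.425. A simulation of 8,000 trials per scenario with identical arms gave 49% to 50% near the peak, while the between-arm tests stayed at about 5%. Each figure applies to one indicator at one time.

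**Step 2: precision of the between-arm comparison.** With SD = 1, the variance of the estimated difference is proportional to:
- follow-up values: 1
- change scores: 2(1 − r)
- ANCOVA on the pre-treatment value: 1 − r², times about 1 + 1/76 = 1.013 for estimating the slope.

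Power at a true difference of 0.5 SD and n = 40 per arm, by normal approximation without the 1.013 factor:

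| r | Variance cut, ANCOVA v. follow-up values | Follow-up values | Change scores | ANCOVA |
|---|---|---|---|---|
| 0 | 0% | 60.9% | 35.2% | 60.9% |
| 0.2 | 4% | 60.9% | 42.4% | 62.6% |
| 0.3 | 9% | 60.9% | 47.2% | 65.0% |
| 0.5 | 25% | 60.9% | 60.9% | 73.3% |
| 0.7 | 49% | 60.9% | 82.3% | 87.9% |

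Simulated power, follow-up values against ANCOVA, was 60.6% v. 60.2% at r = 0, 59.5% v. 61.1% at 0.2, 59.3% v. 71.4% at 0.5 and 60.5% v. 87.1% at 0.7. At r = 0.5 the variance gain equals 40/0.75 ≈ 53 patients per arm. With the slope cost included, the relative variance is 1.013 at r = 0, 1.003 at 0.1 and 0.973 at 0.2, so the worst loss is about 1.3%.

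**Step 3: does the reading of Section 2.9 matter?** If the between-arm test is run on changes, the ANCOVA-to-change variance ratio is (1 − r²)/[2(1 − r)] = (1 + r)/2. This is below 1 for every r below 1, apart from the same small slope cost. Under either reading, ANCOVA is not materially worse.

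**The case against.** A reader might infer more than the article supports.

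- **That the analysis ignores baseline.** The paired test uses it by construction; its fault is that it does not compare arms. The between-arm test may be run on changes, which Section 2.7 makes plausible. A comparison of unadjusted follow-up values at each time is only one reading.
- **That efficacy will be judged by significance in one arm only.** Nothing says so. The percentages in Step 1 are chances of discordant P values. They become errors only if that inference is drawn.
- **That discordance is always common.** It falls sharply when both arms change a lot, as they may if survivors recover on ECMO.
- **That the unadjusted tests, or the unstratified allocation, are faulty.** They are not. Under randomisation the tests are valid, and their standard errors already allow for chance baseline imbalance.
- **That the precision gain is assured.** It depends on r, which the article does not give. At 72 to 96 hours of an acute illness r could be low, and at about 0.2 or less the gain is nil or trivial.

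A further objection is that covariates, repeated-measures models and transformations are commonly left to a statistical analysis plan, which is not shown. That stands against calling their absence an omission, and against faulting the lack of a non-parametric paired test. It does not cover the paired test itself, which is a stated method under a stated significance threshold with no word that it is descriptive.

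**Conclusion.** The point holds as one of interpretation and efficiency, not as correction of an invalid test. The within-group tests cannot show a CRRT effect. If read that way, they would mislead in about 17% to 50% of cases per indicator and time for common changes of 0.1 to 0.5 SD of the differences at n = 40, and seldom for changes of 0.7 SD or more. Baseline adjustment of the continuous indicators reduces variance by about r² relative to comparing follow-up values. This is material from about r = 0.5 and costs at most about 1.3% of variance when r is near zero.

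These sizes rest on assumed values of d and r, roughly normal data and the minimum of 40 per arm; since "the final number will be based on actual recruitment", the actual n may differ. Two limits apply. Adjustment does not by itself deal with values missing after death or early weaning. The r-based gains do not carry over to mortality, weaning or complications, which have no pre-treatment value.

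**What to change.** In Section 2.9, or in the analysis plan if one exists:

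1. State that within-arm changes are descriptive, and drop their P values as evidence of effect.
2. For the continuous indicators (laboratory values, LVEF, SOFA), prespecify the between-arm difference with a 95% CI, from ANCOVA at a named time or one mixed model over the 24 to 96 hour measurements, with the pre-treatment value as covariate. Use the log scale for skewed markers such as NT-proBNP, troponin and lactate.
3. State separately how values missing after death or early weaning will be handled.
4. Optionally, add a secondary analysis of mortality and weaning adjusted for pre-treatment SOFA.

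The cost is wording. Items 1, 2 and 4 use measurements already planned, and SPSS, the named software, fits these models.

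### Section 2.9 allows for skewed data but names only the paired t test for within-group change, which can miss real changes in strongly skewed cardiac and metabolic markers

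*Protocol article*

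**What the plan says.** Section 2.9 (Statistical analysis) sets out the methods for continuous variables in a few lines.

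- **Summary:** "Measurement data are expressed as mean ± standard deviation or median (quartile"), so the plan expects that some variables will not be normal.
- **Between groups:** an independent-samples t test or a Mann-Whitney U test.
- **Within group:** the paired t "test was used for the comparison within the group", with nothing beside it.
- **Level:** "All are two-sided tests", with P "< .05 as the difference is statistically significant".

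Section 2.7 (Observation indicators) asks for changes in laboratory indicators before and after treatment. Its list includes NT-proBNP, "high-sensitivity troponin I, myocardial enzymes", and blood lactate. Section 2.8 schedules these before treatment, at 24, 48, 72 and 96 hours, and 2 hours before weaning, so there are several before/after pairs per marker.

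On size, section 2.3 says "we set the minimum number of people in each group of studies to 40" and that "the final number will be based on actual recruitment".

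**The concern.** The three provisions for continuous data do not fit together. A marker could be judged too skewed for a mean, reported as median (quartile), and compared between arms by a rank test. Its change over time would still be tested by a method built on the mean and SD of the differences.

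For a strongly right-skewed concentration, a few very high values inflate the SD of the raw differences more than they move the mean, and the test loses sensitivity. What is at stake is the description of how these markers move within an arm: with about 40 patients, a real and sizeable fall could be reported as not significant. The plan provides a robust alternative between arms but not here.

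**Working it through.** **The plan's own figure.** The 40 per group cannot be reproduced, because section 2.3 gives no effect size, SD or power. For scale, 40 per arm at two-sided 0.05 gives 80% power for a standardised between-arm difference of (1.960 + 0.842) × √(2/40) = 0.63.

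**Inputs from the document:** n = 40 in a group (2.3); two-sided 0.05 (2.9); paired t test only (2.9).

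**Assumed, because the document gives nothing:** log-normal markers, log-SD σ from 0.5 to 1.5, within-patient correlation ρ = 0.5 on the log scale, and a true halving from before to after.

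**Step 1: signal relative to noise, per pair.**

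- Log scale: d_log = ln 2 / (σ√(2(1 − ρ))), which is 0.693/σ at ρ = 0.5.
- Raw scale, from the log-normal moments with a halved mean: d_raw = 0.5 / √[1.25(e^(σ²) − 1) − (e^(σ²/2) − 1)].

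For σ = 1.0, d_raw = 0.5/√(1.25 × 1.718 − 0.649) = 0.5/1.224 = 0.41, against d_log = 0.69.

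**Step 2: power at n = 40.** For the log scale, power follows from the noncentral t distribution with 39 degrees of freedom and noncentrality d_log × √40 (4.38, 3.51 and 2.92 at σ = 1.0, 1.25 and 1.5). The raw paired t and signed-rank tests were simulated with 20,000 trials per setting, the signed-rank test on raw differences.

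| log-SD | d_raw | d_log | raw paired t | log-scale paired t | signed-rank |
|---|---|---|---|---|---|
| 0.5 | 1.06 | 1.39 | 100% | 100% | 100% |
| 0.8 | 0.58 | 0.87 | 98% | 100% | 100% |
| 1.0 | 0.41 | 0.69 | 86% | 99% | 97% |
| 1.25 | 0.27 | 0.55 | 60% | 93% | 85% |
| 1.5 | 0.17 | 0.46 | 36% | 81% | 69% |

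Separate runs agree within about two points.

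**Step 3: does the low-skew result depend on the size of the change?** Partly. At log-SD 0.5 to 0.8 a halving is so easily detected that every test is near 100%. With the change instead set so that the log-scale test has about 80% power, and correlations of 0.3 to 0.7, the raw paired t test falls short by 6 to 8 points at log-SD 0.5, 23 to 28 at 1.0 and 42 to 48 at 1.5.

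**Step 4: false positives.** With no true change, the raw paired t test rejects in 5.0% of trials at log-SD 0.5, falling to about 3% at 1.5. It is conservative, not inflated.

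**Step 5: the randomised comparison.** For a halving between arms at log-SD 1.0, 1.25 and 1.5, the log-scale t test has about 87%, 69% and 54% power and Mann-Whitney 85%, 66% and 52%, a gap of 2 to 3 points.

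**The case against.** The case for leaving the text alone is substantial. A before/after test within one arm does not estimate the treatment effect. The paired t test produces no excess false positives here. The documents give no skewness for any marker, and log-normal data favour a log-scale test by construction. The article is also silent on transformation, so use of the raw scale is inferred, and a fuller plan might specify otherwise. All of this stands and limits the size of the point. It does not remove the mismatch, because the article positively names a single within-group test beside explicit provisions for non-normal data.

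A reader might infer more. The documents do not support these stronger readings:

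- **The randomised comparison loses much power.** It would only if the t test were used for visibly skewed data. Section 2.9 already names Mann-Whitney, which costs 2 to 3 points.
- **The reported summaries will be driven by extreme patients.** The same sentence that allows mean ± SD offers median (quartile).
- **The choice between t test and Mann-Whitney is left open to follow the P values.** A selection rule is detail that an article may leave to the full plan, and nothing says that the smaller P value will be reported. Even that worst case gives a type I error of about 6.5% to 7.0% for log-normal data and 5.9% for normal data. Choosing by a Shapiro-Wilk test gave 4.4% to 5.2%.

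**Conclusion.** The narrow point holds. Section 2.9 provides for skewed data in its summaries and between-group test but not in its within-group test, while section 2.7 declares before/after change in several concentration markers as an indicator.

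For a true halving in 40 patients, the untransformed paired t test gives up about 13, 33 and 45 percentage points against the log scale at assumed log-SD 1.0, 1.25 and 1.5 (99 − 86, 93 − 60, 81 − 36). Against the signed-rank test the loss is about 11, 25 and 33 points. At log-SD 0.5 to 0.8 it is about 0 to 2 points for a halving, though larger for smaller changes.

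These sizes rest on assumed log-normality, log-SD and correlation. The consequence is missed change in a descriptive, non-randomised comparison. It does not bias the treatment comparison or inflate false positives. That makes it a modest point, worth acting on because the remedy is nearly free.

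**What to change.** In section 2.9, state that NT-proBNP, troponin I, myocardial enzymes and lactate are analysed on the log scale, both between arms and for any within-group change, and reported as geometric mean ratios with 95% confidence intervals. This puts both comparisons of a marker on one scale and gives an interval as well as a P value.

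If the sponsor prefers to keep rank methods, the minimum change is one sentence: for variables summarised by median (quartile), the Wilcoxon signed-rank test replaces the paired t test. In the settings above this recovers most of the lost power, though not all of it.

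The cost is a wording change and a log transform in SPSS, with no new data or patients. The downside is that effects appear as ratios instead of mean differences.
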